## Abstract

**Question:**

Can an electronic health record (EHR) alert that recommends against use of normal saline in patients with a sepsis subphenotype with potential mortality (group D) benefit from balanced crystalloids result in a lower 30-day mortality rate?

**Findings:**

The Precision Resuscitation With Crystalloids in Sepsis (PRECISE) pragmatic randomized clinical trial intends to test a machine learning algorithm to identify and randomize patients with group D sepsis to usual care or the EHR alert intervention (intention-to-treat). The alert should reduce mortality through decreased normal saline use.

**Meaning:**

The PRECISE trial is one of the first precision trials in fluid resuscitation and could impact sepsis resuscitation guidelines.

## Introduction

Intravenous fluids are the most common treatment given to hospitalized patients and are an essential part of resuscitation in patients with sepsis.^1,2,3,4^ Despite the ubiquity of intravenous fluids in sepsis, it remains unknown whether it is better to give balanced crystalloids or normal saline, the 2 major classes of crystalloid fluids. More than a dozen randomized clinical trials have enrolled in total more than 35 000 critically ill patients to compare balanced crystalloids vs normal saline, without finding a consistent mortality benefit from one fluid type vs the other.^5,6,7,8,9^ The one-size-fits-all approach has not worked in fluid resuscitation. Taking a precision medicine approach, a machine learning algorithm that uses bedside vital signs to identify a sepsis subgroup (group D) with a 15% absolute reduction in mortality with balanced crystalloids compared with normal saline has been reported.^10^ Compared with patients in the other subgroups, patients with group D sepsis have relatively lower body temperature, heart rate, and respiratory rate, and are hypotensive. In the US, more than 1.5 million patients develop sepsis every year, and almost all patients with sepsis receive fluids.^10,11^ With such a large patient population, even a small reduction in mortality would have a large public health impact.

The Precision Resuscitation With Crystalloids in Sepsis (PRECISE) trial is a parallel-group, multihospital, single-blind, pragmatic randomized clinical trial in which we apply our machine learning algorithm to identify patients with group D sepsis and randomize them to usual care or intervention, with the intervention being an electronic health record (EHR) alert that nudges clinicians to use balanced crystalloids instead of normal saline. We hypothesize that the alert will reduce 30-day inpatient mortality in the intervention cohort through increased use of balanced crystalloids for patients with group D sepsis.

## Methods

This article was prepared in accordance with the Standard Protocol Items: Recommendations for Interventional Trials (SPIRIT) reporting guideline (Figure 1).^12^ The trial is approved by the Emory University Institutional Review Board, with waiver of informed consent given the minimal risk and impracticability of obtaining consent from patients across all emergency departments (EDs), especially in often-emergency situations of fluid resuscitation. Data will not be deidentified. This trial is believed to pose minimal risk because (1) crystalloid resuscitation with either normal saline or balanced crystalloids is part of routine clinical practice, (2) crystalloids in the trial are only administered when the treating clinician orders crystalloids as part of routine clinical practice, and (3) clinicians will have the final decision on what type of crystalloid to administer even in the intervention arm. An independent data and safety monitoring board (DSMB) will monitor the efficacy and safety of the intervention.

**Figure 1. zoi241019f1:**
[figure not shown]
Schedule of Enrollment, Allocation, Intervention, and Study Closeout ED indicates emergency department; ICU, intensive care unit. ^a^Allocation occurs at the point of clinician initiating a normal saline order. ^b^Intervention is only continued in the ED and ICUs. ^c^The study ends after 30 days of hospitalization, discharge from the ICU, or death in the ICU. ^d^Patients aged 18 years or older presenting to study EDs meet eligibility criteria.

### Study Design

The PRECISE trial is a parallel-group, multihospital, single-blind, pragmatic randomized clinical trial being conducted between 2024 and 2025 in 6 EDs and 16 intensive care units (ICUs) across 6 hospitals in the Emory Healthcare system in Atlanta, Georgia. Study hospitals will enroll patients for at least 12 months, with a potentially longer enrollment period based on sample size reestimation on interim analysis.

The study uses a previously validated algorithm that classifies patients into sepsis subphenotypes based on vital signs obtained in the ED.^10,13,14^ Patients who are classified as having group D sepsis, have a blood culture ordered in the ED, and in whom clinicians initiate a normal saline order will be enrolled in the trial and randomized to usual care vs intervention to compare the primary outcome of 30-day inpatient mortality (Figure 2). The intervention is an EHR alert that nudges clinicians toward ordering balanced crystalloids rather than normal saline, as preliminary data suggest that balanced crystalloids confer a substantial mortality benefit in patients with group D sepsis.

**Figure 2. zoi241019f2:**
[figure not shown]
Screening, Inclusion, Exclusion, and Randomization in the Precision Resuscitation With Crystalloids in Sepsis Trial All adult patients presenting to study emergency departments (EDs) will be screened for enrollment. Based on the vital signs trajectory algorithm, patients will be classified as group A, B, C, or D. Those in group D with a blood culture order in whom a clinician initiates a normal saline order are randomized to usual care or intervention.

### Algorithm Description

The vital signs trajectory algorithm uses vital signs (temperature, heart rate, respiratory rate, and blood pressure) from hospital presentation to classify patients into 1 of 4 subphenotypes (group A, B, C, and D). The algorithm was developed by applying group-based trajectory modeling to vital signs from the first 8 hours of hospital presentation in a cohort of 12 413 patients with suspicion of infection admitted to 4 Emory Healthcare hospitals between January 2014 and December 2017. The algorithm has been validated in a cohort of 8256 patients hospitalized with suspicion of infection between 2018 and 2019 and in 7065 patients hospitalized with COVID-19 between 2020 and 2022. The model was originally developed as a trajectory algorithm, with each subphenotype defined by a set of 5 unique polynomial functions, and with each function describing a vital sign as a function of time from presentation to the hospital (eg, heart rate = β_0_ + β_1_ × time + β_2_ × time^2^). The model has also been tested as an intercept algorithm, using only the first set of vital signs, such that each subphenotype is defined by a set of 5 unique intercepts (eg, heart rate = β_0_). In a secondary analysis of the Isotonic Solutions and Major Adverse Renal Events Trial, there was 80% agreement in classification between the parsimonious intercept model and the criterion standard model, with 90% agreement in specifically group D classification.^6,10^ For the PRECISE trial, the intercept model is being used to classify patients rapidly in the ED with a single set of vital signs, rather than awaiting a full 8 hours of vital signs documentation. Since crystalloid fluid resuscitation starts soon after hospital presentation, the earlier the patient is classified, enrolled, and randomized, the higher the likelihood of observing a benefit from the intervention.

### Population

All adults (aged ≥18 years) presenting to study EDs will be screened. Inclusion criteria are (1) blood culture order in the ED, (2) classification as group D by the vital signs trajectory algorithm, and (3) clinician-initiated normal saline order. Patients who meet the inclusion criteria will be randomized to intervention vs usual care. If study patients are discharged and readmitted to a study hospital during the study period, they will be eligible for reenrollment (Figure 3).

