### Randomization and Allocation

Patients will be randomized to usual care vs intervention using software within the EHR in a simple 1:1 ratio without stratification. Randomization occurs at the point of clinicians initiating a normal saline order.

For patients randomized to the intervention arm, the EHR alert will fire in the ED and the ICU every time normal saline is ordered until the first of the following events: ICU discharge, death, or 30 days of hospitalization. The study intervention will not be continued in the wards. For patients randomized to the usual care arm, there will be no EHR alert in response to fluid orders.

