### Statistical Analysis

The primary outcome is 30-day inpatient mortality compared between the usual care and intervention arms using intention-to-treat analysis (ie, all patients randomized to intervention vs usual care regardless of whether the intervention resulted in a change in fluid choice). The outcome of 30-day inpatient mortality is measured for the index hospitalization. Readmissions and subsequent deaths are not counted toward the primary outcome for the initial hospitalization, but are considered for the readmission hospitalization. The primary analysis will be an assessment for a difference in 30-day inpatient mortality between the arms with a 2-sided *z* test with continuity correction and pooled variance. Thirty-day inpatient mortality rates will be determined using 95% CIs within each study arm and for the observed difference between study arms.

The secondary analysis for primary and secondary outcomes will be a generalized mixed-effects linear model (ie, log-binomial regression model) to estimate the outcome, adjusted for baseline characteristics including age, sex, race and ethnicity, and Sequential Organ Failure Assessment (SOFA) score at randomization. Race and ethnicity will be included in the analyses given potential disparities in treatments and health outcomes by race. The model will also be adjusted for month of the trial, with an interaction term between month and treatment allocation, to evaluate for temporal trends in the efficacy of the intervention (eg, increasing use of balanced crystalloids in usual care could result in decreased separation of the study arms). The hospital to which the patient is admitted will be defined as a random effect (random intercept) in the mixed model. In a separate sensitivity analysis, the hospital to which the patient is admitted will be defined as a fixed effect to evaluate the robustness of the findings. The covariate-adjusted 30-day inpatient mortality rates will be determined using 95% CIs for each study cohort and for the observed difference between the usual care and intervention arms in 30-day inpatient mortality rates. Relative risks will be calculated to measure the degree of association between individual risk factors and 30-day inpatient mortality. The SAS GLIMMIX Procedure, version 9.4 (SAS Institute Inc) will be used to implement the log-binomial regression model.

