### Sample Size and Power Considerations

The power analysis was performed using Emory Healthcare system retrospective data, with mortality estimates based on proportion of normal saline vs balanced crystalloids received. Usual care has an expected mortality rate of 6%, and intervention has an expected mortality rate of 3%. To detect a proportion difference (P2 – P1) of 0.03 (or P1 of 0.03) with 90% power, the number of participants needed will be 1001 in the intervention arm and 1001 in the usual care arm (Table 1). The power was computed using the tests for 2 proportions module from PASS 2023, version 23.0.1 (NCSS LLC).

**Table 1. zoi241019t1:** Power and Sample Size for Hypothesis Tests of the 30-Day Inpatient Mortality Difference Between Usual Care and Intervention^a^

Test	Sample size assumptions and results					
	Usual care P2	Intervention P1	Difference (P2 − P1)	No. of participants		Statistical power, %
				Per group	Total	
1	0.06	0.03	0.03	748	1496	80
2	0.06	0.04	0.02	1863	3726	80
3	0.06	0.03	0.03	1001	2002	90
4	0.06	0.04	0.02	2493	4986	90

^a^
The usual care group mortality rate (P2) is assumed to be 0.06. To detect a proportion difference (P2 − P1) of 0.03 (or P1 of 0.03) with 90% power, the number of participants needed will be 1001 in the intervention arm and 1001 in the usual care arm.

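### Readmitted patients may be enrolled again, but no planned analysis accounts for repeat enrollments and no first-enrollment analysis is prespecified

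*Protocol article*

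**What the plan says.** Under Population, the article states: "If study patients are discharged and readmitted to a study hospital during the study period, they will be eligible for reenrollment". It gives no cap and no minimum interval. Under Randomization and Allocation: "Patients will be randomized to usual care vs intervention using software within the EHR in a simple 1:1 ratio without stratification". It does not say whether this draw is repeated at a second enrollment.

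Under Statistical Analysis, the intention-to-treat set is "all patients randomized to intervention vs usual care regardless of whether the intervention resulted in a change in fluid choice". The primary test is a "2-sided *z* test with continuity correction and pooled variance". For the adjusted model: "The hospital to which the patient is admitted will be defined as a random effect (random intercept) in the mixed model". A sensitivity analysis makes hospital a fixed effect instead. On the outcome: "The outcome of 30-day inpatient mortality is measured for the index hospitalization". It continues: "Readmissions and subsequent deaths are not counted toward the primary outcome for the initial hospitalization, but are considered for the readmission hospitalization".

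Under Sample Size and Power Considerations, the trial is sized in people: "the number of participants needed will be 1001 in the intervention arm and 1001 in the usual care arm".

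The Statistical Analysis section also says that any further outcomes or analyses will be labelled post hoc and treated as hypothesis-generating.

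**The concern.** Once a person can enter more than once, the person and the enrollment are different units. The sample size speaks of participants, while an analysis of everyone randomized, with re-enrollment allowed, most naturally uses enrollments. The z test takes each record as independent. The mixed model takes records as independent given hospital, so it absorbs what patients at one hospital share but not what two stays of one patient share.

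Two things are at stake. First, outcomes that can happen again to the same person (ICU admission, ventilation, vasoactive drugs) will tend to be correlated across that person's stays, and the planned standard errors ignore this. Second, a death soon after the first randomization can be recorded under a different allocation from the one first assigned, or not recorded at all, and no planned analysis shows whether that matters. Because the article labels later additions post hoc, the remedy has to be prespecified to carry weight.

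**Working it through.** **1. The plan's own figure.** Inputs from Sample Size and Power Considerations and Interim Analysis: 6% vs 3%, two-sided alpha 0.05, power 90%. With pooled variance and no continuity correction,

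n = [1.960·√(2·0.045·0.955) + 1.2816·√(0.06·0.94 + 0.03·0.97)]² / 0.03² = (0.5746 + 0.3747)² / 0.0009 ≈ 1001.4 per arm,

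which is 1002 rounded up, against 1001 stated. The plan's number therefore assumes one independent record per person, with no allowance for repeats.

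**2. Where a death goes.** Take a patient randomized to intervention, discharged, readmitted on day 10 and dead on day 15.

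| Readmission | First record | Second record |
|---|---|---|
| Enrolled, drawn to usual care | Survivor, intervention | Death, usual care |
| Enrolled, arm kept | Survivor, intervention | Death, intervention |
| Not enrolled | Survivor, intervention | None; death not counted |

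The third row arises whenever the second stay lacks group D classification, a blood culture order or a saline order.

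**3. Type I error for mortality.** The z test was simulated with 2002 enrollments, 6% mortality in both arms, patient-level frailty, baseline readmission probability of 5%, 10% or 20%, and second-stay risk equal to or double the first (4000 runs per setting). Rejection rates:

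| Setting | No continuity correction | With correction |
|---|---|---|
| No re-enrollment | 0.051–0.059 | 0.042–0.049 |
| Re-randomized | 0.040–0.055 | 0.032–0.046 |
| Arm kept | 0.045–0.049 | 0.037–0.041 |

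There is no inflation. A second enrollment implies survival of the first, so one person cannot contribute two deaths.

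**4. Possible dilution of the mortality difference.** Suppose a share s of the planned deaths falls in re-randomized readmissions and spreads evenly over the arms. Then usual care = 0.06(1 − s) + 0.045s and intervention = 0.03(1 − s) + 0.045s, so the difference is 0.03(1 − s).

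| s (assumed) | Difference, points | Power at 1001 per arm |
|---|---|---|
| 2% | 2.94 | 88.8% |
| 5% | 2.85 | 86.8% |
| 10% | 2.70 | 83.0% |
| 20% | 2.40 | 73.6% |

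This holds only if the 6% and 3% include such deaths, which the article does not say. In the simulation under the planned effect, power without the continuity correction was 87% to 90% when the first-stay alert carried over into the second stay. It was 92% to 98% when each stay responded only to its own allocation, and 90% to 91% with no re-enrollment. The direction is therefore not settled.

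**5. Recurrent secondary outcomes.** Let a fraction f of patients have two enrollments in the same arm, with within-patient correlation ρ. The design effect is 1 + 2fρ/(1 + f), and the share of variance missed is 1 − 1/(design effect). Assumed values, with ρ = 0.5:

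- f = 10%: 1 + 0.10/1.10 = 1.091; variance understated by 8.3%.
- f = 20%: 1 + 0.20/1.20 = 1.167; variance understated by 14.3%.

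With ρ = 0.05 and f = 5%, the design effect is only 1.005. If the arm is redrawn, same-arm pairs add covariance to the variance of the difference and opposite-arm pairs subtract it. With 1:1 draws these roughly cancel on average.

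**6. Unit of the 2002.** If the 2002 are enrollments, the number of people is 2002/(1 + f): 1907, 1820 or 1668 for f = 5%, 10% or 20% (assumed).

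**The case against.** Index-stay inpatient mortality is a stated outcome, and the handling of readmission deaths is written out openly. Any inpatient endpoint omits deaths after discharge, in both arms. That stands: a reader might infer that failing to follow the first randomization for a full 30 days is an error, but the article defines the outcome this way and does not contradict itself.

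A reader might also infer that the primary test is anticonservative. The simulation does not support this.

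Nor can a guessed readmission mortality be set against the expected 3% as deaths missing from the intervention arm. The article gives no readmission rate, and Table 1 is labelled as inpatient mortality. If the arm is kept, the number of repeats per arm depends on survival, but the imbalance is trivial: at 10% re-enrollment, 1001·0.97·0.10 ≈ 97 against 1001·0.94·0.10 ≈ 94.

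No text says that recruitment stops at 2002 enrollments, so a shortfall in people is hypothetical. A fresh draw at each enrollment is perhaps the more natural reading of the randomization text, and it makes the understated variance less likely.

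Finally, handling of repeat patients is often left to an analysis plan, which is not shown here. That argument carries less weight in this case, because the article itself fixes the test, the random effect and the attribution rule, and labels later additions post hoc.

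**Conclusion.** The point holds in a limited form. Re-enrollment is allowed, neither fixed analysis has a patient-level term, no first-enrollment analysis is planned, and the allocation rule for a second enrollment is not stated. For mortality, what remains is an unclear unit of analysis and a possible, unquantified dilution from deaths recorded under a later allocation. The evidence does not support a claim of inflated type I error.

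For recurrent secondary outcomes, standard errors may be wrong. They are too small if the arm is kept, with variance understated by about 8% to 14% under assumed repeat rates of 10% to 20% and correlation 0.5, and by less at lower values. Every repeat rate, correlation and share of moved deaths above is an assumption, since the article gives none. This is a worthwhile, inexpensive improvement and does not invalidate the primary analysis.

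**What to change.** - Keep the index-stay primary outcome.
- State whether a re-enrolled patient is randomized again or keeps the arm, and whether the 2002 are patients or enrollments. If they are enrollments, describe the sample size that way rather than recruit more patients.
- Prespecify an analysis restricted to each patient's first enrollment.
- Wherever all enrollments are analyzed, including the secondary-outcome models, use variance clustered on patient or a patient-level term.
- Add a sensitivity analysis that assigns any death in a study hospital within 30 days of first randomization to that first allocation.

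The cost is some additional analysis and slightly fewer records in the first-enrollment analysis. The data come from the health record extraction already planned, so no new collection should be needed.

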**Figure 3. zoi241019f3:**
[figure not shown]
Enrollment and Randomization in the Precision Resuscitation With Crystalloids in Sepsis Trial Broad inclusion criteria of patients presenting to study emergency departments (EDs) who are classified as group D and have a blood culture ordered. If a clinician initiates a normal saline order, the patients are randomized to usual care vs intervention arms.

### Randomization and Allocation

Patients will be randomized to usual care vs intervention using software within the EHR in a simple 1:1 ratio without stratification. Randomization occurs at the point of clinicians initiating a normal saline order.

For patients randomized to the intervention arm, the EHR alert will fire in the ED and the ICU every time normal saline is ordered until the first of the following events: ICU discharge, death, or 30 days of hospitalization. The study intervention will not be continued in the wards. For patients randomized to the usual care arm, there will be no EHR alert in response to fluid orders.

### Protocol Update

This protocol document was updated on July 4, 2024, and the trial eligibility criteria were modified to match the randomization process as operationalized within the EHR. The original eligibility criteria were patients with group D sepsis with a blood culture ordered in the ED. However, the EHR randomization process occurs only at the point of the clinician initiating a normal saline order. Thus, the updated trial eligibility criteria are patients with group D sepsis with a blood culture order in the ED for whom clinicians initiate an order for normal saline.

### Concealment and Blinding

The PRECISE study is single-blind (ie, patients are blinded to the allocation). In the usual care arm, the clinicians will not receive any feedback from the algorithm and will not know the group classification of their patient. In the intervention arm, if a clinician orders normal saline in a patient classified as having group D sepsis, there will be an EHR alert and the clinician will necessarily be unblinded to the allocation.

